### Participants

#### Patients

This study will include all patients who are 65 years and older in six GP centers. Note that although the ACOVE QIs were meant for vulnerable elders, most of these rules (and certainly the ones that will be selected) will be relevant to all elderly patients, vulnerable or not.

#### Physicians

All GPs in the GAZO centers will be included in the study. All GPs use the same GP information system in their practice.

### Outcome measure

The main outcome measure is the degree of adherence to the automatically verifiable clinical rules (regardless of placement of GPs in teams or centers). Adherence will be calculated in the following ways: 1) as the first primary outcome measure, on which the trial will be powered, we will calculate adherence in terms of the mean pass rate, without distinguishing between specific rules. For this outcome we simply divide the number of times any rule was followed by the number of times any rule was eligible to be followed; 2) we will calculate the pass rates for each rule separately as the second primary outcome measure. The pass rate of a rule is the proportion of times that a rule was followed when it was eligible; and 3) as a secondary outcome we will calculate the number of rules for which there was effect (the pass rate of a rule in its corresponding intervention group was different than in its control group).

We will also calculate the abovementioned measures per patient. Measures pertaining to fall prevention and management will also be investigated separately because fall management comprises a distinct project in itself.

The main outcome measure for the non-verifiable CRs is the degree of adherence as reported by the GPs themselves. In particular, upon receiving advice the GPs can indicate whether they agree (and hence adhere) or disagree (and hence not adhere) with the advice. Adherence will be calculated in the following ways: 1) adherence in terms of the mean pass rate as the first primary outcome measure; 2) adherence for each rule separately, as the second primary outcome; and 3) the number of rules for which there was effect, as a secondary outcome.

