#### Bias control and randomization

Randomization will take place after measurement of baseline data. Every CR will be randomized into two groups of GP teams. Recall that while a patient will usually be seen by only one GP, a GP team consists of two or three GPs sharing care for the same sub-population of patients. When a patient’s official GP is absent, another GP from the team may see the patient.

Based on the baseline measurement and the expected room for improvement, randomization at the GP level is the most appropriate choice in terms of power and also practicality. However, this randomization choice will be adapted in order to control for possible contamination and biases. The discussion below pertains to verifiable CRs because they are the most prone to contamination.

We assume that contamination between GPs, especially in the same center, is relatively high when some GPs receive support for a rule (intervention) and the others none (control). To reduce the probability of this kind of contamination we have two groups of GPs, A and B. Every GP in group A will receive support for a specific subset of supported CRs (subset A) and no support for the rest of the CRs (subset B). By the same token, Every GP in group B will receive support for subset B and no support for subset A. This means that for about half the CRs (subset A) the GPs in group A form the intervention group and the GPs in group B form the control group, and vice versa for the CRs in subset B. All GPs will hence receive some kind of support, which means they do not have to feel that they are in the control group. A disadvantage of this approach is that some CRs are inter-related and improvement in one can explicitly or implicitly lead to improvement in the related one, even if it is not supported. For example, if one CR is supported by giving a reminder to order a laboratory test, and the same laboratory test is required by another CR that is not supported, ordering the laboratory test will be registered as adherence to both CRs. Therefore we will group all inter-related subsets of CRs in either subset A or subset B, elements of the inter-related subsets will hence never appear in both groups.

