#### Statistical unit

The main aim of this study is testing the change in adherence to the automatically verifiable CRs compared to the adherence at baseline of GPs, in terms of the mean pass rate of the rules, and the pass rate per rule. These CRs belong to different domains of geriatric care. Therefore, it is meaningful to consider a relevant subset of the selected verifiable CRs as the main statistical unit in order to calculate the sample size. This means that we eventually aim at increasing the average of the adherence to these CRs.

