### Statistical analyses

Because the included CRs in each trial are not comparable, we do not compare the result of the verifiable CRs trial with the non-verifiable CRs trial. During the analysis plan we therefore did not consider the dependency between the hypotheses behind the two types of trials. The chi-square test will be used to compare individual and sets of CR pass rates between the supported and non supported automatically verifiable CRs, and between the CRs with advice that was framed differently (AP and IN). The binomial test will be used to test whether the number of supported CRs had higher pass rates than the non supported CRs. Statistical analyses will be performed with the R statistical software (R Foundation for Statistical Computing, Vienna, Austria). Standard statistical tests will be used to compare the baseline characteristics of the centers and patients.

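### The first primary outcome pools all rules and is tested without stratifying by rule, so unequal case volume in groups A and B can confound the comparison and inflate the type I error

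*Protocol article*

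**What the plan says.** Under Outcome measure, the first primary outcome for the verifiable rules, on which the trial is powered, is fixed as follows: "we will calculate adherence in terms of the mean pass rate, without distinguishing between specific rules". The calculation is spelled out: "we simply divide the number of times any rule was followed by the number of times any rule was eligible to be followed". Pass rates for each rule separately are the second primary outcome.

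Under Statistical analyses the test is "The chi-square test will be used to compare individual and sets of CR pass rates between the supported and non supported automatically verifiable CRs". No stratification, weighting or adjustment by rule is mentioned.

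The allocation is crossed. Under Bias control and randomization, "for about half the CRs (subset A) the GPs in group A form the intervention group and the GPs in group B form the control". For subset B the roles are reversed. Related rules stay together: "we will group all inter-related subsets of CRs in either subset A or subset B". Under Statistical unit, "These CRs belong to different domains of geriatric care". The unit allocated is the GP team, a pair or triplet. The article describes no balancing of the two groups by size or case volume.

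**The concern.** On the most direct reading of the test, the two sides are:

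- supported: group A on subset A plus group B on subset B;
- unsupported: group A on subset B plus group B on subset A.

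Both sides contain both subsets, but the weight of each subset on each side depends on how many cases groups A and B generate. If group A has more cases, subset A weighs more on the supported side than on the unsupported side. If subset A also has a different underlying pass rate, the crude ratios differ without any effect of the decision support.

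The subsets are built from blocks of related rules in different clinical domains, so equal average pass rates cannot be presumed. With few teams and part-time GPs, equal case volume cannot be presumed either. At stake is the validity of the test on the outcome that sizes the trial.

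**Working it through.** **The plan's own figure.** For 40% against 50%, two-sided 0.05 and power 0.80, the two-proportion formula gives 388 cases per group, or 408 with continuity correction. The stated 408 is reproduced. Two groups make 816 cases.

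**Inputs from the article.** Control pass rate 40%; target difference 10 points; 45 GPs in pairs or triplets, hence about 15 (45/3) to 22 (45/2) teams.

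**Assumptions, not in the article.** 18 teams, 9 per group. Nine pairs and nine triplets make 18 + 27 = 45 GPs. If volume follows GP count, the mean is 2.5 and the SD 0.5, so the team-size CV is 0.2. A CV of 0.4 stands for extra variation, for instance from part-time work. Subset pass rates are chosen to average 40%. There is no intra-team correlation.

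**Algebra with no effect.** With equally frequent subsets:

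- supported rate = w·pA + (1-w)·pB
- unsupported rate = (1-w)·pA + w·pB
- difference = (2w-1)(pA-pB)

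| Subset rates | w = 0.50 | w = 0.55 | w = 0.60 |
|---|---|---|---|
| 45/35% | 0 | 1 point | 2 points |
| 50/30% | 0 | 2 points | 4 points |
| 60/20% | 0 | 4 points | 8 points |

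Unequal subset frequency alone does no harm. With 60/20% and subset A supplying 70% of cases, the difference is 0 at w = 0.50 and 6.8 points (51.1% against 44.3%) at w = 0.60.

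**How often is volume unequal?** SD(w) is about 0.5·CV/√18, which is 0.024 at CV 0.2 and 0.047 at CV 0.4. By the normal approximation, a split of 55/45 or worse has probability about 3% at CV 0.2 and 29% at CV 0.4. A split of 60/40 or worse has probability essentially 0 and about 3%.

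**Type I error by simulation.** Team sizes were drawn from a gamma distribution, teams allocated 9 to 9, and no effect assumed. In each cell, the first figure holds case counts in proportion to team volume and the second also lets them vary at random.

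| Total cases | CV | 45/35% | 50/30% | 60/20% |
|---|---|---|---|---|
| 816 | 0.2 | 5.1 / 5.2% | 5.3 / 6.1% | 6.5 / 8.9% |
| 816 | 0.4 | 5.7 / 5.8% | 7.9 / 8.5% | 17.1 / 18.7% |
| 4,000 | 0.2 | 6.0 / 5.9% | 8.9 / 9.3% | 19.8 / 21.3% |
| 4,000 | 0.4 | 9.4 / 9.1% | 21.0 / 21.0% | 45.0 / 45.3% |

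A Cochran-Mantel-Haenszel test stratified by subset stayed between 4.8% and 5.3% in all of these. The mean crude difference over allocations was about zero.

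**Why more cases make it worse.** The shift depends on team volumes and does not shrink as cases accrue, while the standard error does. A count well above 816 is plausible: six centers × 7,450 patients × about 10% aged 65 or older is about 4,470 patients, with more than 18 verifiable rules expected. The figure of 4,000 cases is illustrative.

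**The case against.** The strongest reply is that the harmful contrast is inferred. The article defines intervention and control within each subset, states its target as the supported set in the intervention group against the control group, and speaks of comparing sets of rules. If subset A were compared between groups A and B, and subset B likewise, the mechanism above would disappear. That reading is possible, but the analysis section does not state it. The comparison there is "between the supported and non supported automatically verifiable CRs", and the outcome counts any rule. A set-wise analysis would also give two results that must be combined into one first primary outcome, and no rule for that is given.

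Other parts of the reply stand:

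- Per-rule pass rates are already a primary outcome and are free of this problem. They could expose a pooled artefact but do not correct it.
- Averaging over many rules may bring the two subset rates close together. At CV 0.2 and a 10-point gap the inflation is negligible at 816 cases.
- A reader might infer large team imbalance from the center range of 3,285 to 10,055 patients. Teams, not centers, are randomized, and a large center may simply have more teams.
- A reader might see two competing targets, because the sample size section says "we eventually aim at increasing the average of the adherence to these CRs". This is loose wording for the mean pass rate, which the outcome section defines. That frequent rules weigh more is a feature of any case-weighted measure, and no error.

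**Conclusion.** The point holds as a should-fix. The unstratified pooled ratio and plain chi-square test are written into the article, so they are not details left to an analysis plan. In the crossed design they are safe only if the groups have equal case volume or the subsets have equal pass rates, and nothing stated secures either.

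The size is uncertain, because it rests on assumed team sizes, subset pass rates and case counts. It ranges from no material inflation to a type I error several times the nominal 5%.

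A reader might infer a systematic bias in favour of the decision support, or a typical shift of 4 to 8 points. Neither is supported. The sign depends on the allocation and averages out. Shifts of that size need a wide gap between subsets, a rare split, or both. The framing trial is less exposed, since both of its groups receive the same rules. The 408 figure is not in question here.

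**What to change.** In Outcome measure and Statistical analyses, define the first primary effect as the difference between supported and unsupported teams within rule, or at least within rule subset. Combine it over rules with Mantel-Haenszel weights or by entering rule as a factor in the model. Report the crude pooled ratio descriptively only. The per-rule outcome can stay as it is.

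The cost is a few sentences of analysis wording. Per-rule pass rates are already planned, so the rule behind each case must be recorded anyway. Stratifying by rule does not deal with clustering of cases by team, which is a separate matter.

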#### Hypothesis about the efficacy of the intervention

A *case* is defined as the situation in which a CR is eligible, meaning that its logical condition is true. Numerous CRs from the same patient can be assessed, and eligibility cases of the same CR are considered to be mutually independent. A power calculation was performed to determine the number of cases needed to detect a minimally clinically relevant effect of the CDSS based on the previously published studies. So far, no studies have been performed that measure the level of adherence to a set of ACOVE QIs in primary care in The Netherlands but Wenger *et al*. [14] showed that a practice-based intervention in the primary-care setting had mean absolute increase pass rates of 21% (from 23 to 44%) and 15% (from 22 to 37%) in two sets of ACOVE CRs.

We assumed 40% adherence in the control group (based on our preliminary baseline analysis) in both verifiable and non verifiable CRs. We can hence make a conservative estimate of an absolute increase of 10% in the mean pass rate of the supported set of CRs in the intervention group compared to the control group. For non-cluster randomization, for a power of 0.80, and two-sided testing at the 0.05 significance level, a total of 408 cases in which CRs are eligible are required in each group.

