### At the level of CRs

In this type of design every CR is randomly assigned to GPs for decision support: some of the GPs will be in the intervention/AP group of the CR (receiving feedback or AP framing about it) and the other GPs will be in the control/IN group for that CR. This means that every GP will be in the intervention/AP group for a randomly selected subset of CRs and in the control/IN group for the complementary set of CRs. It is very probable that every GP will have a unique set of CRs for support and framing, different to any other GP. The advantage is that there are more CRs (expected to be more than 18 verifiable CRs) to be randomly allocated than centers, yielding higher power and hence a shorter minimum follow-up period required to detect an effect. The disadvantage is that contamination between GPs is still possible. However, an additional problem is that the CRs can be inter-related (for example because they pertain to the same condition, such as falls), which leads to contamination, because support for one CR may not only influence the GPʼs behavior for that CR but also for other, related CRs, even if they are not supported. The CRs must therefore be grouped together and all CRs in each group should either be supported or not. In effect, we then have a cluster-randomized trial in which the cluster consists of the CR groups. Hence the power disadvantages apply again due to the low number of resulting clusters (groups of CRs) and the possible need to stratify randomization to have similar GP and patient characteristics for each cluster.

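### Every rule's pass rate is a primary outcome with no stated error control, so the chance of a false primary finding is far above 5% if no rule truly responds

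*Protocol article*

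**What the plan says.** In the Protocol article, Outcome measure, the mean pass rate over all verifiable rules is named "as the first primary outcome measure, on which the trial will be powered". The next item makes each rule primary as well: "we will calculate the pass rates for each rule separately as the second primary outcome measure". For the non-verifiable rules the same section repeats the pattern: "adherence for each rule separately, as the second primary outcome". The number of rules showing an effect is a secondary outcome, and an effect on a rule means that "the pass rate of a rule in its corresponding intervention group was different than in its control group", that is, a difference in either direction.

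The Statistical unit section also names adherence per rule, beside the mean, as part of the main aim.

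The number of verifiable rules appears in the Discussion, under At the level of CRs: "expected to be more than 18 verifiable CRs". No number is given for the non-verifiable rules.

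On testing, Statistical analyses says: "The chi-square test will be used to compare individual and sets of CR pass rates". The only level in the article is in the sample-size paragraph: "two-sided testing at the 0.05 significance level". The only remark on related hypotheses concerns the verifiable trial against the framing trial: "we therefore did not consider the dependency between the hypotheses behind the two types of trials". It does not address the rules within a trial.

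**The concern.** The second primary outcome is not one outcome. In the verifiable trial it is a family of at least 18 comparisons, each carrying primary status beside the mean pass rate. The article does not say whether a trial succeeds on the mean, on any one rule, or on some combination. It gives no divided level, and it does not make the rule tests conditional on the mean.

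Two things are at stake. A trial in which support changes nothing could still report a primary finding on one rule by chance. Conversely, a non-significant result on a rule carries primary weight although the sample size was set for the pooled outcome only.

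**Working it through.** **Inputs.** From Hypothesis about the efficacy of the intervention: control rate 40%, absolute increase of 10 points, power 0.80, two-sided 0.05, 408 cases per group. From At the level of CRs: more than 18 verifiable rules, so *k* = 18 as a round lower figure and *k* = 19 as the literal minimum. Two assumptions are added: each rule is tested at 0.05, since no other level is given, and no rule has a true effect.

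**Step 1: reproduce the stated sample size.** Without continuity correction,

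n = [1.960·√(2·0.45·0.55) + 0.8416·√(0.4·0.6 + 0.5·0.5)]² / 0.10² = (1.3790 + 0.5891)² / 0.01 = 387.3, so 388.

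With continuity correction,

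n = (387.3/4)·[1 + √(1 + 4/(387.3·0.10))]² = 407.1, so 408.

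The stated 408 is reproduced exactly. It is the size for **one** comparison at two-sided 0.05.

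**Step 2: independent rule tests, either direction.** P(at least one false positive) = 1 − 0.95^k.

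- *k* = 18: 1 − 0.95^18 = 60.3%
- *k* = 19: 1 − 0.95^19 = 62.3%

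The expected number of false findings is 18 × 0.05 = 0.90, or 19 × 0.05 = 0.95. Adding the mean pass rate, simulated as the combined statistic of the same rules, gives 61.2% and 63.2%.

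**Step 3: correlated rule tests, either direction.** With a common correlation ρ between normal test statistics, a shared standard normal factor F and c = 1.96,

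P = 1 − E_F{[Φ((c − √ρ·F)/√(1−ρ)) − Φ((−c − √ρ·F)/√(1−ρ))]^k}.

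| ρ | 18 rules | 19 rules |
|---|---|---|
| 0.1 | 58.9% | 60.8% |
| 0.3 | 50.9% | 52.5% |
| 0.5 | 39.8% | 40.9% |

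**Step 4: only errors in favour of support.** The rate per rule is then 0.025. Under independence, 1 − 0.975^18 = 36.6% and 1 − 0.975^19 = 38.2%. Dropping the second Φ term in Step 3 combines this with correlation: at ρ = 0.5 the result is 19.9% and 20.5%.

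**Step 5: information per rule.** From Step 1, 80% power for 40% versus 50% on one rule takes about 388–408 cases per arm **for that rule**, which is the whole of the stated requirement. If the level were 0.05/19 = 0.00263 (Bonferroni, for illustration), the number rises to 732 per arm without continuity correction, and the familywise error is 1 − (1 − 0.00263)^19 = 4.9%.

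**Framing trial.** *k* is not stated, so Steps 2 to 4 cannot be evaluated. The structure is the same.

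**The case against.** **The analysis plan is not shown.** It could set a per-rule level or an adjustment, and 0.05 per rule is inferred from the sample-size paragraph. This stands as a condition on the figures. It does not remove the point, because the protocol itself makes every rule primary.

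**First and second primary imply an order.** They do rank the outcomes, but nothing makes the second depend on the first. Even a gate on the mean would not control error among the rules once it is passed.

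**The plan has a summary across rules.** Statistical analyses includes a binomial test on how many rules favour support. It does not govern which individual rules may be claimed.

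**A false success is not shown to be more likely than not.** A reader might infer this from the 60–62%, but the documents do not support it in general. That figure counts rules on which support looks harmful, which fits the article's definition of an effect but is not a success for the system. Favourable errors alone give 37–38%. The article also says that rules can be inter-related, and correlation lowers every figure.

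**Per-rule power is not known to be negligible.** An even split of 408 over 18 rules gives 22.7 cases per arm and about 10% power for 10 points, but 408 is a minimum and the even split is an assumption. The GAZO description gives about 7,450 × 6 × 10% = 4,470 patients aged 65 or older. If each had one eligible case, spread evenly, there would be 4,470/(2 × 18) = 124 per arm per rule and about 35% power. The true count is not stated, so neither figure can be asserted.

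**Per-rule adherence belongs to the main aim.** This also stands, and it bears on the remedy: demotion is not required.

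**Conclusion.** The point holds. The protocol makes each rule's pass rate primary in both trials and states no control of error across the rules. For 18–19 verifiable rules tested at two-sided 0.05 with no true effects, the familywise error is:

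- about 60–62% if the tests are independent and either direction counts;
- about 41% at a common correlation of 0.5;
- about 37–38% counting only errors in favour of support, under independence, and about 20% if that is combined with a correlation of 0.5.

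Every case is far above 5%. The correlation values are assumptions, the rule count is the article's expectation, and each chi-square test is taken to hold its nominal level. If some rules do respond, false claims remain possible for the others.

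No figure can be given for the framing trial. Only the mean pass rate is powered, so a non-significant single rule should not be read as absence of effect unless that rule has cases approaching 388–408 per arm. The test of the mean pass rate is not undermined by this point.

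**What to change.** State that the primary conclusion of each trial rests on the mean pass rate alone. Allow a claim about an individual rule only if that test is significant at two-sided 0.05, and then with Holm adjustment across all rules in that trial. Otherwise report per-rule pass rates as estimated differences with intervals. Keeping the per-rule rates as a gated second primary outcome, or moving them to secondary, are both acceptable; the first leaves the stated aim intact. State the final number of rules in each trial.

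Trial status says that data collection has started, so the change should be documented and dated before analysis. No change to allocation, system or data is needed. The cost is fewer single-rule claims and lower power for each rule.
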